# A single-blind, dose escalation, phase I study of high-fluence light-emitting diode-red light (LED-RL) on human skin: study protocol for a randomized controlled trial

**DOI:** 10.1186/s13063-016-1518-7

**Published:** 2016-08-02

**Keywords:** Light-emitting diode-red light, LED-RL, High-fluence, Phototherapy, Skin fibrosis, Wound healing, Scar, Keloid, RCT

## Abstract

**Background:**

Skin fibrosis is involved in a variety of pathologic conditions ranging from scar formation secondary to surgery or trauma to immune-mediated processes. Skin fibrosis is a significant international health problem with an estimated incidence of greater than 100 million people affected per year worldwide with few effective treatment options available. Preliminary in vitro data generated by our research group suggests that red light can function as a stand-alone treatment for skin fibrosis. To our knowledge, no prior clinical trials have been performed to determine the safety of high-fluence (dose) light-emitting diode-red light (LED-RL) phototherapy. The goal of this study is to evaluate the safety of LED-RL fluences from 160 J/cm^2^ up to 640 J/cm^2^ in healthy subjects.

**Methods/design:**

This is a single-blind, dose escalation, randomized controlled, phase I study to evaluate the safety of high-fluence LED-RL on human skin. The protocol for dose escalation requires subjects be enrolled sequentially in groups of five. Within each group, three subjects will be randomized to LED-RL phototherapy and two subjects randomized to mock therapy. Subjects in group 1 randomized to LED-RL phototherapy will receive the maximum recommended starting dose (160 J/cm^2^). LED-RL dose will be escalated in subsequent groups (320 J/cm^2^, 480 J/cm^2^ and 640 J/cm^2^). The maximally tolerated dose (MTD) is defined as the dose level below the dose producing unacceptable but reversible toxicity and is considered to be the upper limit of subject tolerance. After either a MTD has been established, or the study endpoint of 640 J/cm^2^ has been achieved, an additional 27 LED-RL phototherapy subjects (for a total of 30) and 18 mock therapy subjects (for a total of 20) (determined randomly) will be enrolled. Each subject will receive a total of nine procedures, three times per week for three consecutive weeks.

**Discussion:**

This study may provide important safety information on the effects of high-fluence LED-RL phototherapy on human skin and help facilitate future phase II studies to evaluate the efficacy of high-fluence LED-RL as a potential noninvasive, safe, portable, at-home therapy for treatment of skin fibrosis.

**Trial registration:**

ClinicalTrials.gov NCT02630303. Registered on 9 December 2015.

**Electronic supplementary material:**

The online version of this article (doi:10.1186/s13063-016-1518-7) contains supplementary material, which is available to authorized users.

## Background

Skin fibrosis is involved in a variety of pathologic conditions ranging from scar formation secondary to surgery or trauma, such as hypertrophic or keloid scars, to immune-mediated processes, such as scleroderma and chronic graft-versus-host disease. Skin fibrosis is a significant international health problem with an estimated incidence of greater than 100 million people affected per year worldwide with few effective treatment options available [1]. In addition, skin fibrosis is a significant socioeconomic burden due to the functional, aesthetic, and psychosocial impacts on patients’ lives [1, 2]. A consumer survey of the American Society for Dermatologic Surgery (ASDS) reported that over 50 % of survey respondents considered treatment with laser and light therapy to improve scar appearance and skin discoloration [3]. In 2014, members of the ASDS performed more than 2.7 million procedures using lasers, lights, and energy-based devices [4]. Lasers and light-based devices have gained increased attention and their use has expanded amongst dermatologists and patients alike due to minimal downtime associated with phototherapy procedures and convenient at-home use of many devices.

Many of the currently available treatments for skin fibrosis have certain pitfalls and limitations. For example, immunosuppressive agents such as systemic corticosteroids may lead to serious systemic side effects. Anti-fibrotic agents such as intralesional steroids, 5-fluorouracil, and bleomycin are invasive, painful, and have associated skin and systemic effects [5–9]. Ultraviolet (UVA/UVA1) and UVB/narrowband UVB phototherapy generate UV-induced deoxyribonucleic acid (DNA) damage that is associated with skin cancer and/or photoaging [10].

Recently published clinical observations indicate that red light (600 to 700 nm) in combination with other modalities such as photosensitizers in combined red light photodynamic therapy can lessen skin fibrosis [11–13]. Red light has a penetration depth of up to 4 mm, which allows it to reach the entirety of the dermis where skin fibrosis occurs [14, 15]. These findings make red light a promising treatment modality that is noninvasive, unlikely to cause systemic side effects, and does not generate pro-carcinogenic DNA damage as may occur in UV light treatment.

Preliminary in vitro data generated by our research group suggests that red light may function as a stand-alone treatment for skin fibrosis, eliminating the side effects of chemical photosensitizers [16, 17]. Furthermore, commercially available light-emitting diode-red light (LED-RL) units exist and are already Food and Drug Administration (FDA)-cleared for other dermatological uses (such as for improvement of rhytides and acne) [18, 19]. Thus, clinical translation for the use of LED-RL phototherapy in skin fibrosis could occur relatively quickly following demonstration of its safety and efficacy. Developing LED-RL phototherapy as a treatment modality would represent an important advance in therapy for scarring conditions, without the side effects associated with current treatment options.

To our knowledge, no prior clinical trials have been performed to determine the safety of high-fluence (dose) LED-RL phototherapy. High-fluence LED-RL phototherapy is phototherapy with fluence >160 J/cm^2^ per treatment session. The goal of this study is to establish the safety of LED-RL fluences from 160 J/cm^2^ up to 640 J/cm^2^ in healthy subjects, and to help facilitate future phase II efficacy studies of high-fluence LED-RL phototherapy as an innovative, safe, and efficacious treatment modality.

## Methods/design

### Hypothesis

High-fluence LED-RL phototherapy is safe on human skin.

### Study endpoints

This study will end if the maximally tolerated dose (MTD) is identified or if the predefined study endpoint of 640 J/cm^2^ is reached.

### Study design and subject population

This is a single-blind, dose escalation, randomized controlled, phase I study to evaluate the safety of high-fluence LED-RL phototherapy on human skin. The maximum recommended starting dose (MRSD) of 160 J/cm^2^ is based upon previously published maximum doses of LED-RL phototherapy used in clinical studies that demonstrated clinical safety with no adverse events [18, 19]. The study endpoint of 640 J/cm^2^ was chosen due to feasibility, as this dose corresponds to 2 hours of LED-RL phototherapy, and we anticipate decreased subject compliance with LED-RL exposures longer than 2 hours in duration. Additionally in prior studies, the 640 J/cm^2^ dose demonstrated increased anti-fibrotic properties in vitro compared to lower doses of LED-RL [17].

The protocol for dose escalation requires subjects to be enrolled sequentially in groups of five (three subjects randomized to LED-RL phototherapy and two subjects randomized to mock therapy). As this is a single-blind study, subjects will be blinded to the procedure (LED-RL phototherapy or mock therapy).

Subjects in group 1 randomized to LED-RL phototherapy will receive the MSRD of 160 J/cm^2^. The LED-RL dose will be escalated in subsequent groups using the classical method for dose escalation as described by Spilker: starting with dose (X) increased by an equal amount (in this instance: X = 160 J/cm^2^, 2X = 320 J/cm^2^, 3X = 480 J/cm^2^, and 4X = 640 J/cm^2^) [20]. Common expected procedural side effects are mild and are expected to last less than 24 hours, which include warmth, redness (erythema), and swelling (edema). The MTD is defined as the dose level below the dose producing unacceptable but reversible toxicity and is considered to be the upper limit of subject tolerance. Unacceptable but reversible toxicities (adverse events) for this study include: second-degree or higher skin burning or blistering, erythema lasting more than 24 hours, severe swelling, pain, ulceration, change in sensation, and/or muscle weakness. If one or more subject experiences any of these adverse events, then this is the dose one above the MTD, and we will not proceed with this dose or escalate the dose.

After either an MTD has been established, or the study endpoint of 640 J/cm^2^ has been achieved, an additional 27 LED-RL phototherapy subjects (for a total of 30) and 18 mock therapy subjects (for a total of 20) (determined randomly) will be enrolled to satisfy Hanley’s Rule of Three, such that it can be concluded with 95 % confidence that fewer than 1 person in 10 will experience an adverse event [21]. Of the larger cohort, the study will be stopped if adverse events determined to be device-related equal or exceed 30 %. Each subject will receive a total of nine LED-RL phototherapy or mock therapy procedures, three times per week for three consecutive weeks. The phototherapy regimen of three procedures per week is a standard phototherapy protocol [22]. Each subject will receive a US$50 check for completion of 1 week (total of US$150 for completion of entire study), and subjects will receive a prorated amount in the event of withdrawal from study.

This study has a sample size of up to 65 subjects. Subjects will be recruited from the Sacramento Veterans Affairs (VA) Medical Center. As detailed in the inclusion criteria, subjects may be of any sex, age, and ethnicity. The Standard Protocol Items: Recommendations for Interventional Trials (SPIRIT) checklist, flow diagram, and trial registration data are available as Additional files 1, 2, and 3.

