### Specifications of LED-RL phototherapy and mock therapy hand-held unit

The LED-RL light source is a commercially available Omnilux New-U hand-held LED-RL phototherapy unit (provided by Photo Therapeutics, Carlsbad, CA, USA), and is FDA-cleared for treatment of periorbital rhytides (crow’s feet) and may be placed in direct contact with the skin [23]. The mock therapy unit, also provided by Photo Therapeutics, Carlsbad, CA, USA, only generates warmth and does not emit LED-RL. The LED has a 4.7 cm × 6.1 cm rectangular aperture and emits visible red light (633 nm ± 30 nm) at a power density of 360.2 W/m^2^ at room temperature in direct contact with the photometer.

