### Study procedure

The study procedure for subjects receiving LED-RL phototherapy and for subjects receiving mock therapy is identical with the exception of utilizing the LED-RL phototherapy unit or the mock therapy unit for the randomized subjects in their respective groups. After confirming subject identity, screening for study eligibility, and obtaining written Institutional Review Board (IRB)-approved informed consent, the subject will be taken to a private clinic examination room at the Dermatology Clinic in Sacramento VA Medical Center. The subject’s nondominant proximal anterior forearm will be cleaned with alcohol pads. A surgical marking pen will be used to outline the procedure area at the start and completion of every visit. The LED-RL phototherapy or mock therapy hand-held unit will be held in place and in direct contact with the clean area using nonadhesive tape (ACE elastic bandage or similar) during the procedure. All subjects will be provided with protective eyewear to use at LED-RL phototherapy and mock therapy sessions. The research team will be observing the procedure and assessing for any safety issues during and immediately post-procedure. Photographs will be taken pre-and post-procedure at each clinic visit to record and assess for common expected procedural side effects and adverse events, and to ensure uniformity of procedure location at every clinic visit.

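### At the stated irradiance, 2 hours delivers about 259 J/cm², not 640, so the dose labels and the MTD may be off by a factor of 2.5

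*Protocol article*

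**What the plan says.** Under *Study design and subject population*, the protocol article escalates fluence in equal steps: "X = 160 J/cm^2^, 2X = 320 J/cm^2^, 3X = 480 J/cm^2^, and 4X = 640 J/cm^2". It explains the ceiling of 640 J/cm² by saying that it "was chosen due to feasibility, as this dose corresponds to 2 hours of LED-RL phototherapy", and adds that "we anticipate decreased subject compliance with LED-RL exposures longer than 2 hours in duration". A second reason given there is the stronger in vitro effect at that dose.

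Under *Specifications of LED-RL phototherapy and mock therapy hand-held unit*, one LED source is described, emitting red light "at a power density of 360.2 W/m^2^ at room temperature in direct contact with the photometer". Under *Study procedure*, the "hand-held unit will be held in place and in direct contact with the clean area", which is the same contact geometry as the measurement.

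The article gives no second irradiance, no session length for the three lower doses, and no calibration that links the output figure to the 2 hours.

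**The concern.** Irradiance, exposure time and fluence are tied by one identity, so any two fix the third. The article states all three for the top dose, and they do not agree.

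Fluence is the quantity being escalated. It is also the scale on which the MTD is expressed, the study endpoint, and the exposure to which the safety conclusion will be attached. The Discussion expects later phase II trials to use this study when choosing a dose. If the labelled fluence is not the delivered fluence, the safety statement describes an exposure that was not tested. If it is, the session length that justified the ceiling is wrong.

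**Working it through.** **Inputs**

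- Irradiance: 360.2 W/m² (device specifications). Since 1 m² = 10,000 cm², this is 360.2 / 10,000 = 0.03602 W/cm².
- Top dose and its time: 640 J/cm² in 2 h = 7200 s (study design).
- Dose ladder: 160, 320, 480, 640 J/cm² (study design).
- Aperture: 4.7 × 6.1 = 28.67 cm² (device specifications), used only to test another reading of the output figure.

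**Trying to reproduce the plan's figure**

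Fluence (J/cm²) = irradiance (W/cm²) × time (s).

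- 0.03602 × 7200 = 259.3 J/cm². The stated 640 is not reproduced.
- Ratio: 640 / 259.3 = 2.47. The delivered dose would be 259.3 / 640 = 40.5% of the label.
- Time needed for 640 J/cm²: 640 / 0.03602 = 17,768 s = 4.94 h (4 h 56 min).
- Irradiance needed for 640 J/cm² in 2 h: 640 / 7200 = 0.0889 W/cm² = 889 W/m².

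**Other readings of the output figure**

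- Read as 360.2 mW/cm²: 0.3602 × 7200 = 2593 J/cm².
- Read as 360.2 mW in total, spread over the aperture: 0.3602 / 28.67 × 7200 = 90 J/cm².

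Neither gives 640.

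**Across the dose ladder**

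Only the top dose is given a time. For the lower levels, the second and third columns below assume one device and time proportional to dose. The last column is label / 0.03602 / 60.

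| Label (J/cm²) | Minutes, pro rata to 2 h | Delivered at 360.2 W/m² (J/cm²) | Minutes to reach the label at 360.2 W/m² |
|---|---|---|---|
| 160 | 30 | 65 | 74 |
| 320 | 60 | 130 | 148 |
| 480 | 90 | 195 | 222 |
| 640 | 120 | 259 | 296 |

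**What follows in each case**

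(a) *Output is 360.2 W/m² and sessions are timed on the 2-hour equivalence.* Labels are overstated 2.47-fold. The top level (259) does not reach nominal level 2 (320). The first two levels (65 and 130) fall below the 160 J/cm² mark above which the Background calls a dose high-fluence.

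(b) *Output is 360.2 W/m² and sessions run to the labelled fluence.* The labels hold, but three of the four levels exceed 2 hours. Nine top-dose sessions take 9 × 4.94 = 44 h per subject, against 9 × 2 = 18 h.

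(c) *Output is really about 889 W/m² and sessions last 2 h.* The labels hold and the device section is wrong. Anyone who set exposure times from the printed output would then deliver 2.47 times the label: 160 × 2.47 = 395 J/cm² at the starting dose and 640 × 2.47 ≈ 1,580 J/cm² at the top.

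**The case against.** The best reply accepts the arithmetic and limits what follows from it. The 2-hour remark explains why escalation stops at 640 J/cm²; it is not a dosing instruction. The article specifies dose as fluence and nowhere says that therapy sessions run for 30, 60, 90 or 120 minutes. Delivered doses differ from their labels in case (a). In case (b) only the feasibility argument fails. In case (c), if staff work from 2 hours, the fault is a misprinted specification with no effect on dose. A condensed article may also leave exposure tables and session logs to the full protocol.

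Much of this stands. The article does not show which figure is wrong, so mislabelled doses are a possibility and not a demonstrated fact. The lower-level figures in case (a) rest on an assumption, and missing operational detail is not itself an error.

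It does not remove the contradiction, which lies between two stated figures and not in an omission. The 2 hours are linked to expected subject compliance, so they describe a session in this trial and not some other lamp. Measurement and use share contact geometry, and nothing in the article suggests that the room-temperature qualifier could hide a 2.5-fold difference. No fuller document can make both figures true.

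**Conclusion.** The concern holds. The stated irradiance and the 2-hour equivalence for 640 J/cm² are incompatible by a factor of 2.47: 259 J/cm² in 2 hours, or 4.94 hours for 640 J/cm². This uses only the article's own figures and the definition of fluence, and it is certain.

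What remains open is which figure is wrong. The statement that all dose labels and the MTD are overstated about 2.5-fold depends on the output being 360.2 W/m², on sessions being timed from the 2-hour equivalence, and, below the top dose, on one device with linear timing. Under the alternatives, either the feasibility rationale or the device specification is wrong.

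Each case needs a correction, and the error sits on the quantity that defines the dose levels. It must be fixed before any dose label is relied on.

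**What to change.** Reconcile the study design section with the device specifications:

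- Measure the irradiance of each study unit in contact, over a run as long as the longest session.
- State the exposure minutes for each dose level as fluence divided by that irradiance.
- Correct whichever of irradiance, time or fluence label proves wrong, everywhere it appears.
- Log start and stop times for each session, and report the MTD and the safety conclusion in delivered fluence. The log goes beyond removing the contradiction, but it lets delivered dose be verified.

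No particular dose is proposed here.

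The basic cost is a photometer check, a short table of exposure times and a protocol clarification. No redesign or extra subjects are needed to resolve the contradiction. Further cost depends on the answer. The article reports that enrolment began in January 2016, so in case (a) delivered doses would have to be reconstructed for subjects already treated and their groups relabelled. In case (b) the feasibility argument must be rewritten and the burden of sessions of nearly 5 hours faced openly. In case (c) only the device specification changes, provided that no session was timed from the printed output.

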### Safety assessment

All subjects will be asked to record any common expected procedural side effects and adverse events in a subject diary of adverse events for the entire duration of study participation. A review of the subject’s diary will occur at each clinic visit prior to the start of the procedure. Subjects will be called weekly to monitor for any adverse events. Subjects with adverse events will receive standard medical care outside of the scope of this study. Ancillary and post-study care is available at the General Dermatology Clinic, Sacramento VA Medical Center, but no additional compensation will be provided to those who suffer harm from study participation. All common expected procedural side effects and adverse events will be described in the Case Report Form. The Data Safety Monitoring Board, which includes three board-certified dermatologists, one phototherapy nurse, and two clinical research coordinators, will convene monthly to review and assess any study safety issues. The principal investigator (PI: JJ) has access to interim results and may make the decision to stop a subject from study participation due to safety reasons.

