### Statistical analysis

Statistical analysis will be performed using Statistical Package for Social Sciences (SPSS) or similar. Quantitative data will be presented as mean ± standard deviation and range while qualitative data will be presented as number (*n*) and percentage (%). Student’s *t* test will be used to determine if there is a significant difference in the rate of common expected procedural side effects and adverse events between the LED-RL phototherapy group and the mock therapy group. *P* <0.05 will be used as statistically significant. Data analysis relating to protocol nonadherence and any missing data will be consulted with the biostatistics service at UC Davis Clinical and Translational Science Center.

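### Three safety decision rules are worded too loosely: the 1-in-10 conclusion needs 0 events in 30, the 30% stop has an ambiguous base, and the escalation trigger names no arm

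*Protocol article*

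**What the plan says.** All three rules stand in the protocol article, Methods/design, under Study design and subject population.

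- **Safety conclusion.** After escalation, 27 LED-RL and 18 mock subjects are added, giving totals of 30 and 20. The reason given is the Rule of Three, so that it can be concluded with 95% confidence that "fewer than 1 person in 10 will experience an adverse event". No condition on the number of events seen is attached.
- **Stop in the expansion.** The next sentence reads "Of the larger cohort, the study will be stopped if adverse events determined to be device-related equal or exceed" 30%. It does not say which arm or arms make up that cohort, or whether events or subjects are counted.
- **Escalation trigger.** Each group has "three subjects randomized to LED-RL phototherapy and two subjects randomized to mock therapy". The rule is "If one or more subject experiences any of these adverse events, then this is the dose one above the MTD", after which that dose is dropped and escalation stops. The MTD itself is defined by reference to the dose that produces the toxicity.

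Three other places bear on the reading. The same section names the arm where only one is meant: "Subjects in group 1 randomized to LED-RL phototherapy will receive the MSRD" of 160 J/cm². The device section says the mock unit "only generates warmth and does not emit LED-RL". Under Safety assessment, "All subjects will be asked to record any common expected procedural side effects and adverse events", and Statistical analysis compares side effects and "adverse events between the LED-RL phototherapy group and the mock therapy group". Under Blinding, the investigator and coordinators know the allocation.

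**The concern.** These sentences decide the expansion dose, whether the trial stops, and what may be claimed at the end. Each can be followed as written and give a result the study would not want.

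1. The 1-in-10 conclusion is stated as something the sample size delivers. It is delivered only by a particular outcome, 0 events in 30, and the adjacent stopping rule allows the cohort to finish with other outcomes.
2. If the larger cohort is read as both arms, subjects who receive no red light dilute a stop meant to protect those who do.
3. If any subject can fire the trigger, an event in a mock subject sets the LED-RL MTD one level below the current dose. In group 2, for example, the expansion would then run at 160 J/cm² even if 640 J/cm² were tolerable.

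**Working it through.** **The plan's own figures.** Total: 4 × 5 + 27 + 18 = 65, as stated. Rule of Three: 3/30 = 0.10. Exact one-sided 95% upper limit with 0 events: 1 − 0.05^(1/30) = 0.0950. The smallest n that gives a limit below 0.10 with 0 events is ln 0.05 / ln 0.90 = 28.4, so 29. The sample size of 30 is right.

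**1. The conclusion when events occur.** The exact (Clopper-Pearson) one-sided 95% upper limit for x events in n = 30 is the 0.95 quantile of Beta(x + 1, 30 − x).

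| Events in 30 | Upper limit |
|---|---|
| 0 | 9.5% |
| 1 | 14.9% |
| 2 | 19.5% |
| 8 | 43.0% |

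Eight is the most allowed if the stop is at 9 of 30. One event is enough to lose the 10% bound; with one event, 46 subjects would be needed to keep it.

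**2. The 30% stop.** The smallest count with x/n ≥ 0.30 on each possible base:

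| Base | 0.30 × n | Limit |
|---|---|---|
| 27 (added LED-RL) | 8.1 | 9 |
| 30 (all LED-RL at the expansion dose) | 9.0 | 9 |
| 45 (all added) | 13.5 | 14 |
| 50 (both arms) | 15.0 | 15 |

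On a base of 50, 14 events do not stop the study. With 0, 2 or 4 of them in mock subjects, the LED-RL arm can hold 14/30 = 47%, 12/30 = 40% or 10/30 = 33%.

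The documents give no event rates. Assume a true LED-RL rate of 40% and mock rates of 0%, 5% and 10%, with X ~ Bin(30, 0.40) and Y ~ Bin(20, mock rate):

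- P(X ≥ 9) = 0.906.
- P(X + Y ≥ 15) = 0.175, 0.296 and 0.427.

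**3. The escalation trigger.** Assume a listed event occurs with probability p per subject in both arms, with no light toxicity, and let q = 1 − p. A trial stops on a mock-only event in group k if all five subjects in each earlier group are clear, the three LED-RL subjects in group k are clear, and at least one of its two mock subjects is not:

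Σ (k = 1 to 4) of (q⁵)^(k−1) · q³ · (1 − q²)

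| Assumed p | Stop on a mock-only event | of which in group 1 | Pass all four groups, all subjects count (q²⁰) | Pass all four groups, LED-RL only (q¹²) |
|---|---|---|---|---|
| 1% | 7.2% | 1.9% | 82% | 89% |
| 5% | 23.7% | 8.4% | 36% | 54% |
| 10% | 29.7% | 13.9% | 12% | 28% |

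The last column also shows what naming the arm does not cure: 1 − q¹² = 11%, 46% and 72% of trials would still stop early on background events in LED-RL subjects.

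**The case against.** **The trigger has a clear intended meaning.** The MTD is tied to a dose that produces toxicity, a mock subject receives no light dose, and the staff applying the rule know the allocation. This largely stands. A reader might infer that the plan lets mock events set the MTD by design; the documents do not support that. Recording events in all subjects and comparing the arms shows only that mock events are collected. What remains is that the operative sentence names no arm and has no step at which judgement is applied.

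**A mock event is not meaningless.** The mock unit warms the skin and is strapped on like the active one, for sessions that the article puts at 2 hours at the top dose. A burn or pain in a mock subject could therefore bear on heat or prolonged contact. This stands, and is why such events should go to the safety board and not be ignored.

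**Much of the trigger problem survives the fix.** Correct. Background events in LED-RL subjects can still produce a false MTD. The absence of a planned level below 160 J/cm² follows from any group 1 event, in either arm. Neither comes from the arm wording.

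**The 30% stop does have a base.** It does, so it would be wrong to say that none is given. The base is ambiguous, and limiting the count to device-related events does not settle it, since the mock unit is also a device. The 47% case needs a base of 50, no mock events and no action from a safety board that meets monthly.

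**Naming the Rule of Three implies zero events.** It does for a reader who knows the method. Nor do a precision target and a stopping limit contradict each other. But the sentence presents the conclusion without its condition, directly before a rule that allows events.

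**The event rates are assumptions.** They are. Many listed events are severe and subjects are screened for photosensitivity, so the 1% row may be nearer the truth than the 10% row.

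**Conclusion.** The point holds as a wording defect in three stated decision rules, not as an error in the sample size or the escalation scheme.

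- **The conclusion** is the firmest part and rests on no assumed rate: below 10% only with 0 of 30.
- **The stop** ranges from 9 to 15 events by reading. The drop from 91% to between 18% and 43% in the chance of stopping rests on an assumed 40% LED-RL rate, mock rates of 0% to 10%, and 9 of 30 against 15 of 50.
- **The trigger** is the weakest part. The LED-RL reading is likely; only the literal reading gives mock-only stops in about 7% to 30% of trials, at assumed rates of 1% to 10% in both arms and no light toxicity.

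The changes should be made, because the rules fix dose, stopping and the main safety claim, and rewording them costs almost nothing.

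**What to change.** Three changes under Study design and subject population:

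1. **Conclusion.** Add: *This conclusion applies only if 0 of the 30 LED-RL subjects have an adverse event. Otherwise the exact one-sided 95% upper limit will be reported.*
2. **Stop.** Replace with: *The study will be stopped if device-related adverse events occur in 30% or more of LED-RL subjects at the expansion dose (9 of 30).* This also settles that subjects are counted, not events.
3. **Trigger.** Begin the sentence: *If one or more LED-RL subjects experience any of these adverse events.* Add that a listed event in a mock subject is referred to the safety board, since it may bear on heat or contact.

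The one-event trigger stays. There are no extra subjects or visits. The small downside is that a mock event no longer halts escalation automatically; it goes to the board, which already meets monthly. The change does not address false MTDs from background events in LED-RL subjects or the lack of a level below 160 J/cm².
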